## **11. Data Analysis and Statistical Analysis**

### **11.1. General Principles of Statistical Analysis**

#### **11.1.1. Definition of Analysis Sets**

The efficacy analysis of this clinical trial will primarily use the Full Analysis Set (FAS), with the Per-Protocol Set (PPS) used for supplementary verification as needed.

- 1) FAS: Adhering to the Intention-To-Treat (ITT) principle, the FAS includes all randomized subjects who have taken the investigational product at least once and for whom efficacy data have been collected at least once. Data from subjects not meeting pre-established criteria will be excluded. The exclusion criteria for the FAS analysis are as follows:
  - Violation of inclusion or exclusion criteria
  - Subjects who did not take the investigational product even once
  - Subjects who did not provide any data after screening
- 2) PPS: The PPS consists of subjects from the FAS who have a medication compliance of 70% or more, have completed all procedures as specified in the protocol, and have no major protocol violations that could affect the results. The definition of major violations follows the details in Section 7.1 of this protocol.

The safety analysis will include data from all subjects who have taken the investigational product at least once after randomization and for whom a safety assessment was performed. The analysis will be conducted based on the group to which subjects were actually assigned.

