| Statistical Analysis    | 
• General Principles of Statistical Analysis
 
 
1. Definition of Analysis Sets 
For the analysis of data from this clinical trial, efficacy analysis will primarily use the Full Analysis Set (FAS) as the main method, and the Per Protocol Set (PPS) analysis will be used as a supplementary confirmation when necessary.
 
 
1) The FAS is defined according to ITT principle, which includes all randomized subjects who received at least one dose of the investigational product and have at least one post-baseline efficacy measurement. All data obtained from these subjects will be included in the analysis. However, subjects who do not meet a pre-established criteria will be excluded. The exclusion criteria for the FAS are as follows: 
 
i. Subjects who violate the inclusion or exclusion criteria
 
ii. Subjects who did not take the investigational product even once
 
iii. Subjects who did not provide any data after screening
 
 
 
2) The PPS analysis set consists of a subset of subjects from the FAS who have a drug compliance rate of at least 70% of the total investigational product dose, completed the entire trial process as specified in the protocol, and have no major protocol violations that could affect the results. The definition of major violations is based on the content described in section 7.1 of this protocol.
 
 
For the safety analysis of the data obtained from this clinical trial, all data from subjects who received at least one dose of the investigational product after randomization and underwent a safety evaluation will be included in the analysis. For safety analysis, subjects will be analyzed in the group they actually received treatment in.
 
 
 |

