### 5.3. Sample Size

#### 1) Sample Size

|                                           | GGTCS group | Placebo group | Total |
|-------------------------------------------|-------------|---------------|-------|
| Final efficacy population (PP)            | 70          | 70            | 140   |
| Population considering dropout rate (20%) | 88          | 88            | 176   |

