## **7. Dropout and Early Termination Criteria**

### **7.1. Dropout**

Dropout refers to the premature termination of a subject's participation before completing all study procedures. The investigator may stop the treatment and observation and withdraw the subject, and the subject may voluntarily withdraw from the study at any time. A subject who meets any of the following criteria may be withdrawn from the study at the discretion of the principal investigator or responsible investigator. In the event of any of the following, the administration of the study drug and the trial itself may be discontinued, leading to withdrawal.

- 1) If a subject is confirmed to violate the inclusion/exclusion criteria after screening.
- 2) If a systemic disease, not discovered during pre-administration screening, is found in the subject.

- 3) If the investigator determines that continuous administration is inappropriate due to a serious adverse event in the subject.
- 4) If the investigator determines that continuous administration is inappropriate due to the severity of an adverse event.
  - Subjects who discontinue early due to an adverse event may receive appropriate treatment for the event if necessary.
- 5) If the investigator determines that the subject's symptoms have worsened and other treatment is required.
- 6) If the subject or their legal representative withdraws consent for participation in the clinical trial or requests to stop the administration of the investigational product (due to unsatisfactory therapeutic effect during the trial period).
- 7) If the subject's visits and follow-up are not possible.
- 8) If the subject violates the clinical trial protocol or leaves the hospital without permission, making it difficult to continue the trial.
- 9) If the subject takes any prescribed medication or over-the-counter medication that could affect the study's outcome (e.g., safety, pharmacokinetic properties) without the supervising physician's instruction during the clinical trial period (all periods after screening).
- 10) If the subject's medication compliance is significantly low, at less than 70%.
- 11) Other cases where the investigator judges the continuation of the clinical trial to be inappropriate.

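### The PPS takes its major violations from Section 7.1, a list of dropout reasons that includes outcomes; this is a minor defect confined to the supplementary set

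*Protocol*

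**What the plan says.** Protocol Section 11.1.1 makes the FAS the main efficacy set and uses the PPS to support it where needed. A PPS member must belong to the FAS, have at least 70% compliance, have completed every protocol procedure, and have no major protocol violation capable of influencing the results. For that last condition Section 11.1.1 states: "The definition of major violations follows the details in Section 7.1 of this protocol". The synopsis repeats it in slightly different words: "The definition of major violations is based on the content described in section 7.1 of this protocol".

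Section 7.1 is headed Dropout and opens with a definition of that term: "Dropout refers to the premature termination of a subject's participation before completing all study procedures". It then gives eleven circumstances in which the investigator has discretion to withdraw a subject. Among them are:

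- item 3: "If the investigator determines that continuous administration is inappropriate due to a serious adverse event in the subject"
- item 4: "If the investigator determines that continuous administration is inappropriate due to the severity of an adverse event"
- item 5: "If the investigator determines that the subject's symptoms have worsened and other treatment is required"
- item 6: withdrawal of consent or a request to stop the product, with the bracketed reason "due to unsatisfactory therapeutic effect during the trial period"

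The section does not use the term major violation and does not rank violations by importance.

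**The concern.** A per-protocol set is meant to remove departures from the planned conduct of the trial. An adverse event, a worsening cold or dissatisfaction with the effect is not a departure. Each can happen to a fully compliant subject, and worsening and lack of effect are closely related to the primary endpoint, the change in WURSS-21-K total score to Day 7. Calling them major violations makes PPS membership depend on the response to treatment.

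The PPS is the only supporting efficacy set the protocol names. Under Section 11.1.3 last observation carried forward (LOCF) applies only in the FAS, so readers are likely to use the PPS as a check on the LOCF-based result. If its membership depends partly on outcome, agreement or disagreement with the FAS becomes harder to interpret. The reference also does not work as a definition. Item 8 speaks of violating the protocol without saying which violations are major, and item 11 is open-ended judgement.

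**Working it through.** The point concerns a definition, so no figure in the protocol changes. The sample size, which Section 5.3 labels as the PP population, reproduces:

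- 2 × (1.960 + 0.842)² × 21² / 10², with unrounded normal quantiles, = 69.227, rounded up to 70 per group.
- 70 / (1 − 0.20) = 87.5, rounded up to 88 per group, 176 in total.

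**Step 1. Is Section 7.1 a list of violations?**

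| Item in 7.1 | Nature |
|---|---|
| 1 eligibility violation found after screening | deviation, but already excluded from the FAS |
| 2 systemic disease missed at screening | baseline condition |
| 3, 4 adverse events | outcome |
| 5 worsening that needs other treatment | outcome |
| 6 consent withdrawn or request to stop, unsatisfactory effect named | outcome, or subject's choice |
| 7 visits or follow-up not possible | loss to follow-up |
| 8 protocol violation that hampers continuation | deviation, but circular as a definition |
| 9 unsupervised medication | deviation |
| 10 compliance below 70% | deviation, already a PPS criterion |
| 11 other investigator judgement | undefined |

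Four of the eleven items (1, 8, 9, 10) are conduct deviations. Two of those four (1 and 10) duplicate criteria stated elsewhere. Four items (3 to 6) are outcomes or outcome-driven.

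**Step 2. Whom do the other PPS criteria already remove?**

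- Completion: Section 7.3 defines a completed subject as one with all planned visits and assessments and no discontinuation or withdrawal. A subject actually withdrawn under items 3 to 6 fails this.
- Compliance: if all 21 packets were due, 14 / 21 = 66.7% fails and 15 / 21 = 71.4% passes. A subject who stops early for an adverse event or lack of effect after 14 or fewer packets fails this.
- Missing Day 7 score: with LOCF limited to the FAS, a subject without that score has no imputed value to bring to a PPS analysis of the primary endpoint.

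**Step 3. Who is left for the reference alone to remove?** Only a subject who meets a 7.1 item, is not withdrawn before completing, and has at least 70% compliance. This is possible because withdrawal under 7.1 is discretionary and because the schedule places a dropout status check at Visit 3. For example, a subject takes the full supply, records the Day 7 WURSS-21-K and attends Visit 3, where the investigator judges that symptoms have worsened and other treatment is needed. That subject passes completion and compliance and has an observed primary endpoint, yet meets item 5 and so counts as a major violator under the reference.

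**Step 4. How many such subjects?** The protocol gives an overall 20% dropout allowance but no rate by reason, and no rate for subjects who meet an item and still complete. The size of the reference's own effect cannot be computed.

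**The case against.** The strongest reply is that the reference is loose wording with almost no consequence. Delete it and PPS membership would barely change, because completion, compliance and the FAS-only LOCF rule already remove most of these subjects. Items 3 to 5 need an investigator's determination and item 6 needs a request to stop or withdrawal of consent, so few who meet them will go on to complete everything. This stands, and it limits the weight of the point.

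A second reply is that a narrower reading is open. The condition concerns protocol violations capable of influencing the results, the synopsis only bases the definition on 7.1, and an adverse event is not naturally a violation. This stands in part: the text is ambiguous. But nothing exempts items 3 to 6, and worsening is the item most easily judged to influence the results.

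A third reply is that a statistical analysis plan may define violations properly. That does not answer the point. The protocol has not left the definition open; it has fixed it to the wrong section, and a differing plan would contradict it.

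A reader might infer that the cross-reference shifts the PPS treatment difference by a calculable amount, for instance by removing every subject below some improvement cut-off in a normal model. The documents do not support this. Section 7.1 has no score threshold, and such a model would also count subjects whom the completion criterion removes anyway.

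**Conclusion.** The concern holds in a limited form. Section 11.1.1 and the synopsis both define PPS violations by a list of discretionary dropout reasons, four of whose eleven items are outcomes or outcome-driven. The added effect of the reference is confined to subjects who meet an item but complete with adequate compliance. Its size is unknown, and its direction would depend on which arm loses more such subjects and on how they responded. The main source of outcome-related selection in the PPS is the completion criterion, not the reference.

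A reader might also infer that the primary result is compromised, or that the PP label in the sample size table makes the PPS decisive. Neither follows. The FAS is the main efficacy set and its definition does not use Section 7.1, while the label concerns sizing only. Severity is minor. The conclusion assumes that the reference is applied as written and that the completion criterion is read in line with Section 7.3.

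**What to change.** In Section 11.1.1 and the synopsis:

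1. Replace the reference to Section 7.1 with an explicit list of conduct deviations: eligibility violation, unsupervised or prohibited medication, wrong product received, and compliance below 70%.
2. State that adverse events, worsening and unsatisfactory effect are not in themselves protocol violations.
3. Restate or justify the completion criterion, so that a subject with adequate compliance and an observed Day 7 WURSS-21-K score is kept unless a listed deviation applies.
4. Describe the PPS as a completer-type sensitivity analysis and interpret it as such.

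Section 7.1 can stay as it is for its own purpose, withdrawal. The change costs a paragraph of wording, with no new data or visits, and the PPS becomes slightly less clean. Some selection will remain: subjects who worsen and take prohibited medication still leave the PPS, and those with no Day 7 score still contribute nothing to its primary comparison. That is why step 4 is needed.

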#### **11.1.2. General Principles of Analysis**

- 1) All statistical analyses will be based on a two-sided test with a significance level ( $\alpha$ ) of 5%.
- 2) The statistical software SAS® Version 9.4 will be used for all analyses.

- 3) Continuous data will be presented as mean and 95% confidence interval, while categorical data will be presented as frequency and percentage.
- 4) If necessary, subgroup analysis will be conducted by categorizing subjects based on their baseline characteristics at the screening or baseline visit.

### **11.1.3. Handling of Missing Data**

Missing data will be imputed using the Last Observation Carried Forward (LOCF) method. This method will only be applied to efficacy endpoints in the FAS.

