## 3. Handling of Missing Data

In this study, missing values will be imputed using the Last Observation Carried Forward (LOCF) method. This imputation will only be applied to efficacy endpoints in the FAS.

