Based on the 1:1 allocation ratio between the treatment and control groups, the required number of subjects per group is 70. Considering a 20% dropout rate for this clinical trial, a total of 176 subjects (88 per group) are needed.

Subjects will be recruited from multiple centers, with a target of 88 subjects from Daejeon University Daejeon Korean Medicine Hospital, and 44 subjects each from Kyung Hee University Korean Medicine Hospital and Pusan National University Korean Medicine Hospital. However, the number of subjects recruited per center may vary depending on the recruitment speed. The final allocation of subjects per center will be re-evaluated by the Central Data Management (DM) team at the midpoint (50%) of the total study period, based on the recruitment speed of each center. If the number of subjects per center changes, an independent statistician will generate new codes as needed, considering the block size, and these will be reflected in the randomization schedule for each center. Investigational products will be provided to each study site based on their initial number of subjects. Additional products for sites with increased subject numbers will be provided by the drug manufacturer (National Institute of the Korean Medicine Development) according to the newly generated randomization codes. Sites with a reduced subject number will be instructed to discard the remaining randomization codes.

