#### 2) Prohibited Concomitant Medications

- During the clinical trial period, the use of the following medications that may affect symptoms is prohibited. If the use of a prohibited medication is necessary, the subject must discontinue the clinical trial.
  - ① Antibiotics, antiviral agents, steroids, decongestants, antihistamines, antitussives/expectorants, and other medications expected to relieve nasal congestion.
  - ② Medications administered for the same therapeutic purpose as the investigational product or those that may affect the improvement of nasal congestion symptoms.
  - ③ Medications containing the same active ingredients (Puerariae Radix, Ephedrae Herba, Zizyphi Fructus, Cinnamomi Ramulus, Paeoniae Radix, Glycyrrhizae Radix et Rhizoma, Zingiberis Rhizoma Crudus, Cnidii Rhizoma, and Magnoliae Flos), even if they are not used for the same therapeutic purpose as the investigational product.

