### 9.3. Rescue Medication

Subjects are permitted to take Acetaminophen if they experience fever (38°C or higher) or extreme pain. However, the maximum dose is limited to 6 tablets/day and 18 tablets/week (500mg/tablet). Subjects who complain of a high fever of 39°C or higher will be withdrawn from the study.

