## **11.2. Statistical Analysis of Outcome Measures**

### **11.2.1. Primary Outcome Measures**

Hypothesis: The mean change in the WURSS-21-K total score (symptom score + quality of life score) from baseline to Day 7 is not equal between the test group and the control group.

The analysis will be conducted using an ANCOVA model with the group as the effect and the baseline WURSS-21-K total score as a covariate. If necessary, other variables that show a statistical difference in demographic characteristics or that could affect cold symptoms will also be included as covariates. The least-square mean (LSM) difference between the control and test groups, its 95% confidence interval, and the p-value will be presented.

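### LOCF as the primary method for Day 7 does not suit an illness that improves daily: it shrinks a true effect, and biases the estimate if unresolved dropout differs between arms

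*Protocol*

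**What the plan says.** Protocol 11.1.3 reads "Missing data will be imputed using the Last Observation Carried Forward (LOCF) method" and adds "This method will only be applied to efficacy endpoints in the FAS". The synopsis repeats the rule: "missing values will be imputed using the Last Observation Carried Forward (LOCF) method". The FAS is the main efficacy set (11.1.1), "with the Per-Protocol Set (PPS) used for supplementary verification as needed".

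The primary endpoint (11.2.1) is "The mean change in the WURSS-21-K total score (symptom score + quality of life score) from baseline to Day 7", analysed by ANCOVA with group and baseline score. The WURSS-21-K is recorded every day in a diary (10.2.2, 10.3.1.1).

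On losses, section 5.3 says "Considering a 20% dropout rate for this clinical trial, a total of 176 subjects (88 per group) are needed". Section 9.2 says "If the use of a prohibited medication is necessary, the subject must discontinue the clinical trial", and section 9.3 says "Subjects who complain of a high fever of 39°C or higher will be withdrawn from the study". Section 7.1 allows withdrawal, at the investigator's discretion, for worsening symptoms, adverse events, unsatisfactory effect and other reasons.

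**The concern.** LOCF treats the score after dropout as constant. The protocol's own material says otherwise: section 3 describes a self-limiting illness, and Table 1 in section 5.3 shows a large fall on placebo. A subject last seen early and still ill is given a Day 7 score that ignores the recovery still to come. A subject withdrawn for worsening may instead be given a score from before the worsening, which is too favourable.

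The primary estimate then depends partly on who left, when, and from which arm. Lack of effect could remove more placebo subjects, and intolerance more GGTCS subjects. These two shift the estimate in opposite directions, so LOCF cannot be relied on to be conservative.

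**Working it through.** **1. The plan's own figure.** Two-sided 5%, power 80%, difference 10, SD 21 (section 5.3): 2 × (1.960 + 0.842)² × 21² / 10² = 69.2, so 70 per arm. 70 / 0.8 = 87.5, so 88 per arm and 176 in total. Both reproduce.

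**2. Inputs and assumptions.**
- From section 5.3: SD 21, 88 per arm, and a placebo fall of 29.09 (baseline-adjusted; the unadjusted fall is 66.48 − 33.33 = 33.15).
- Assumed, because the documents do not say: the fall is linear over 7 days and the same in both arms when there is no drug effect; the last score is on Day k; dropout rates are given by arm. All 88 per arm enter the analysis.
- Standard error of the difference: 21 × √(2/88) = 3.17.

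**3. Error for one unresolved dropout.** Recovery not counted = 29.09 × (7 − k)/7. This is 24.9 points for a last score on Day 1, 20.8 on Day 2, 16.6 on Day 3 and 8.3 on Day 5.

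**4. No true effect, unequal dropout.** False difference b = gap in dropout proportion × recovery not counted. Type I error = 1 − Φ(1.96 − b/3.17) + Φ(−1.96 − b/3.17).

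| Last score | Gap 5 points | Gap 10 points | Gap 20 points |
|---|---|---|---|
| Day 1 | 1.25; 6.8% | 2.49; 12.4% | 4.99; 35.0% |
| Day 2 | 1.04; 6.2% | 2.08; 10.1% | 4.16; 25.9% |
| Day 3 | 0.83; 5.8% | 1.66; 8.2% | 3.32; 18.3% |
| Day 5 | 0.42; 5.2% | 0.83; 5.8% | 1.66; 8.2% |

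With the unadjusted fall of 33.15, a 10-point gap gives 0.95 points (Day 5; 6.0%) to 2.84 points (Day 1; 14.6%).

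**5. Front-loaded recovery.** Daily scores were simulated (88 per arm, 1,500 runs per scenario, Day 7 change SD 21, last score on Day 1 to 3) and analysed by the planned ANCOVA after LOCF. With an exponential course, a 10-point gap gives about 1.2 points and 7% to 8% type I error; a 20-point gap gives about 2.4 points and 13%. The linear course in the same simulation gives 2.0 points and 9%, and 4.2 points and 26%.

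**6. Equal dropout, true effect 10.** The estimate becomes 10 × [(1 − p) + p × k/7]. With p = 0.20 and k = 3 this is 8.86; 8.86/3.17 = 2.80, so power is about 80%. In the simulation (Day 1 to 3) the estimate is 8.5 with power 72% (linear) and 9.3 with power 82% (front-loaded). With no true effect, no false difference beyond simulation error appears.

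**7. Unequal dropout, true effect 10, k = 3.**
- 25% lost on GGTCS, 15% on placebo: 39.09 × 0.857 − 29.09 × 0.914 = 6.9, power about 59%.
- The mirror case: 39.09 × 0.914 − 29.09 × 0.857 = 10.8.

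**8. An alternative on the same data.** A missing-at-random estimate built by sequential regression on the daily scores had bias of at most 0.2 points under no effect, and returned 9.9 to 10.2 when the truth was 10. Only its point estimate was computed. Dropout in this simulation was random within arm, which also left a completers-only analysis nearly unbiased. The result says nothing about withdrawal that depends on unseen worsening.

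**The case against.** The strongest reply is that the larger figures rest on inputs outside the documents. There is no dropout by arm, no timing and no daily course. At the protocol's single figure of 20%, taken as equal in both arms, LOCF creates no false difference and power can stay near the planned 80%. That stands, though early dropout with a linear course brought it down to 72%.

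A reader might go on to infer three stronger things, none of which the documents support.

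- That any imbalance produces a false difference that matters. A 5-point gap, or dropout late in the week, moves type I error only to between about 5% and 7%.
- That every dropout is held at a sick score. Section 9.1 has subjects stop the drug once symptoms disappear; if their diary ends there, a near-zero score is carried forward, which is reasonable. Worsening withdrawals may err the other way, and the calculation does not model them.
- That 20% of the FAS will be imputed. Section 5.3 uses 20% to inflate from a per-protocol population. That set also loses subjects for compliance below 70% (9.4), who may have a complete Day 7 diary. Eligibility violators and subjects with no data after screening leave the FAS altogether (11.1.1). The share imputed may well be lower.

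It is also tempting to say that the standard error is wrong because imputed values count as observed. Neither the direction nor the size of that was established, so it is not part of this point.

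Finally, sensitivity analyses are often left to an analysis plan that is not shown. Their absence is not the complaint. The protocol itself fixes the primary method, and the PPS, a completer set used only as needed, does not test it.

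**Conclusion.** The point holds as a poor choice of primary method that should be changed. LOCF conflicts with the course of illness that the protocol describes. If unresolved dropout is equal in rate and timing, the cost is attenuation: a true 10 becomes about 8.5 to 9.3 if 20% lack a Day 7 score. If it differs by arm, the estimate is biased. For a 10-percentage-point gap with no true effect, the false difference is about 0.8 to 2.5 points (8% to 25% of the target effect) and type I error about 6% to 12% with a linear course, or about 1.2 points and 7% to 8% with a front-loaded one. It favours GGTCS if placebo loses more, and works against GGTCS in the reverse case.

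The mechanism is certain from the text. The size is not: it rests on assumed arm splits, timing and course, and on applying the 29.09-point fall to the seven days of this trial.

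**What to change.** In 11.1.3, 11.2.1 and the synopsis, replace LOCF as the primary method with a likelihood-based repeated-measures model, or multiple imputation, on the daily WURSS-21-K diary scores. Adjust for baseline and take the Day 7 group contrast as the primary estimate. Keep LOCF as a supportive analysis.

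Add a missing-not-at-random sensitivity analysis, delta-adjusted or reference-based, because withdrawal for worsening or for prohibited medication makes missing-at-random uncertain. State that diary scores recorded up to Day 7 after study drug is stopped will be used. The treatment-stopping rules stay as they are.

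The cost is wording, some extra programming, and reliance on missing-at-random in the primary analysis, which the sensitivity analysis is there to probe. The diary is already collected. The change should be made before unblinding.
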